**Methods:**

To develop the new method for engaging patients and their caregivers in guideline development, we will first conduct interviews with experts on RAM, guideline development, patient engagement, and patient-centeredness and engage with Duchenne patients and caregivers to identify how RAM should be modified for the purposes of patient engagement and what rating criteria should patients and caregivers use to provide their input during the process of guideline development. Once the new method is piloted, we will test it by conducting two concurrently run patient/caregiver panels that will rate patient-centeredness of a subset of DMD care management recommendations already deemed clinically appropriate and necessary. The ExpertLens™ system—a previously evaluated online modified Delphi system that combines two rounds of rating with a round of feedback and moderated online discussions—will be used to conduct these panels. In addition to developing and testing the new engagement method, we will work with the members of our project’s Advisory Board to generate a list of best practices for enhancing the level of patient and caregiver involvement in the guideline development process. We will solicit input on these best practice from Duchenne patients, caregivers, and clinicians by conducting a series of round-table discussions and making a presentation at an annual conference on Duchenne.

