Second, ratings of patient-centeredness collected during the EL panel process will be analyzed quantitatively to determine the existence of consensus among participants. It is recommended that every Delphi study determine how consensus will be defined among participants before the data collection begins [42]. One of the EL features is its use of the RAM [27] to automatically determine the group decision (eg, whether a particular care management strategy was deemed patient-centered) for each round 1 item, which is displayed in round 2 and is also calculated after round 3. This process, identical to that used in determining appropriateness of different DMD care management strategies, begins with determining the existence of disagreement among participants using the following a priori process. EL automatically (1) calculates the value of interpercentile range (IPR), or the range of responses that fall between the 70th and the 30th percentiles; (2) calculates the value of the interpercentile range adjusted for symmetry (IPRAS), which is a measure of dispersion for asymmetric distributions; and (3) compares the values of IPR and IPRAS to see if there is disagreement. Disagreement is said to exist if IPR>IPRAS [27,50]. Disagreement among participants automatically produces an uncertain decision. If, instead, there is no disagreement among panelists, the value of the median will determine if the group decision is positive, negative, or uncertain. If the median is within the upper tertile of the 9-point response scale (response categories 7-9), then the decision is positive, meaning that a care management approach is considered to be patient-centered. If the median is within the lower tertile of the 9-point response scale (response categories 1-3), then the decision is negative, meaning that a care management approach is considered to be not patient-centered. A median that lies within the middle tertile (response categories 4-6) produces an uncertain decision. We will use this approach to determining consensus on the patient-centeredness of care management strategies in both EL panels using round 1 and round 3 rating data.

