To determine the replicability of online panel ratings, we will adopt the following a priori analytic approach originally developed by Shekelle and colleagues [51] to analyze reproducibility of in-person panel ratings. We will first examine round 3 determinations of patient-centeredness for each care management strategy and identify the proportion of strategies receiving positive, negative, or uncertain determinations. Then, we will determine the pairwise percentage of agreement between the two panels and use *t* tests to identify any statistically significant differences in panel ratings. Because the distribution of ratings may be nonnormal, we will conduct sensitivity analyses using the Wilcoxon rank sum, a nonparametric method. We will treat a 70% agreement as an indicator of acceptable reproducibility, which is at least as good as that of in in-person panels [51]. Finally, we will calculate kappa coefficients comparing the determinations made by the two panels across items. If the kappa statistic is at least moderate (.41-.60), we will consider the online approach to be a reliable mode of collecting patient-centeredness ratings using the modified RAM approach [52]. This threshold is conservative; previous research shows that the reproducibility of both in-person [51] and online [31] panel findings is rarely better than moderate.

Besides comparing ratings of patient-centeredness, we will also focus on participant experiences after round 1 (survey) and round 3 (Delphi). As in earlier studies [31], we will pool the data across the two EL panels and look at the average response to each satisfaction question asked in round 1 and round 3. We will consider a mean value of 5 (agree slightly) and higher on the 7-point positively worded agreement scale to be an indicator of a generally positive opinion. Depending on sample size, we may conduct exploratory factor analyses to identify constructs that capture participant experiences and opinions about the new online system. To explore differences in participant satisfaction and perceived usefulness of the online approach after rounds 1 and 3, we will use a paired *t* test. We anticipate greater satisfaction and perceived usefulness after round 3 but a higher level of perceived participation burden.

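### Two replicability pass marks, 70% raw agreement and kappa of at least .41, are set with no rule on which governs, and they can conflict when determinations cluster in one category

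*Protocol article*

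**What the plan says.** The replicability analysis is in the Data Analysis section. The round 3 result for each care management strategy is one of three categories: the plan will "identify the proportion of strategies receiving positive, negative, or uncertain determinations". A positive result requires no disagreement and a high median: "If the median is within the upper tertile of the 9-point response scale (response categories 7-9), then the decision is positive".

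Two criteria are then applied to the same determinations:

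- Raw agreement: "we will determine the pairwise percentage of agreement between the two panels", followed by "We will treat a 70% agreement as an indicator of acceptable reproducibility".
- Kappa: "we will calculate kappa coefficients comparing the determinations made by the two panels across items", followed by "If the kappa statistic is at least moderate (.41-.60), we will consider the online approach to be a reliable mode". Of this mark the article adds "This threshold is conservative".

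The article does not say whether both marks must be met, which one decides, or what is concluded if one passes and the other fails. It states no expected share of positive determinations and no number of items. The items are described in the abstract as "a subset of DMD care management recommendations already deemed clinically appropriate and necessary".

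**The concern.** Raw agreement and kappa answer different questions once determinations are unevenly spread. If most items are positive in both panels, the panels agree on many items whether or not they respond to the same item-level differences. Kappa removes that part; the 70% mark does not. With two marks and no precedence, the conclusion can depend on which one is quoted, and that choice could be made after the data are seen.

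Replicability is one of the stated tests of the new method. Followed as written, the 70% rule could label two panels with unrelated item-level determinations as acceptably reproducible.

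**Working it through.** **Inputs.** From the Data Analysis section: the 70% mark, the .41 mark and the three categories. Not in the article, and therefore assumed: the share of items positive (60% to 85% below), how the remaining items are divided (split equally between the other two categories, or all in one), equal category shares in the two panels, and the number of items (20 as the main case; 10 and 40 as alternatives). The two marks are cut-offs, so there is no derived figure to reproduce.

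**Formulas.** With Po the observed agreement and Pe the chance agreement, kappa = (Po − Pe)/(1 − Pe). With equal shares in both panels, Pe is the sum of the squared category shares.

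**Step 1: when does 70% agreement also meet kappa .41?** Setting Po = .70 and kappa = .41 gives Pe = (.70 − .41)/(1 − .41) = .29/.59 = .49. If the non-positive items split equally, this means no more than about 66% positive. If only two categories are used, Pe is at least .50, so 70% agreement gives kappa of at most (.70 − .50)/.50 = .40 and never reaches the mark.

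**Step 2: agreement needed for kappa .41.** This is Pe + .41(1 − Pe). In each pair, the first figure is for an equal split of the remainder and the second for all of it in one category.

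| Positive | Pe | Kappa at 70% agreement | Agreement needed for kappa .41 |
|---|---|---|---|
| 60% | .440 / .520 | .46 / .38 | 67% / 72% |
| 70% | .535 / .580 | .36 / .29 | 73% / 75% |
| 80% | .660 / .680 | .12 / .06 | 80% / 81% |
| 85% | .734 / .745 | −.13 / −.18 | 84% / 85% |

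For example, at 80% positive with an equal split, Pe = .64 + .01 + .01 = .66 and kappa = (.70 − .66)/.34 = .12. Pe itself equals .70 at 82.8% positive (equal split) or 81.6% (one category).

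**Step 3: how often do unrelated panels reach 70%?** For independent panels the number of agreeing items is binomial with probability Pe. With 20 items, 70% is at least 14 agreements.

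| Positive | 10 items | 20 items | 40 items |
|---|---|---|---|
| 60% | .09 / .21 | .02 / .08 | .001 / .02 |
| 70% | .24 / .33 | .10 / .20 | .03 / .08 |
| 80% | .54 / .60 | .45 / .53 | .36 / .47 |
| 85% | .74 / .76 | .73 / .77 | .75 / .80 |

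**Step 4: does kappa guard against this?** Largely. In a simulation with assumed shares of 80/15/5% (positive/uncertain/negative; Pe = .64 + .0225 + .0025 = .665) and 20 items, unrelated panels reached 70% agreement in about 47% of runs but kappa .41 in only 2%. With true kappa .41, agreement passed while kappa failed in about 44% of runs, so conflict is not confined to unrelated panels. The standard deviation of kappa at 20 items was about .17 to .25 over true values from 0 to .41. A point estimate near .41 is therefore imprecise: with true kappa .20, it passed in about 17% of runs.

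**Step 5: a concrete table.** Take 20 items, with each panel giving 17 positive and 3 uncertain. If 15 are jointly positive, 1 jointly uncertain and 4 discordant, then Po = .80, Pe = .85² + .15² = .745 and kappa = .055/.255 = .22: the 70% mark passes and kappa fails. With the same margins but only 2 discordant items, Po = .90 and kappa = .155/.255 = .61: both pass.

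**The case against.** The strongest reply has four parts.

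*The skew is not established.* A reader might infer that the two marks give opposite verdicts because items already judged appropriate and necessary will be rated mostly positive. The article does not support that as a prediction. Panels rate patient-centeredness, a different property. The Introduction notes that recommendations clinicians endorse may be unacceptable to patients, and Data Collection plans discussions of strategies that are appropriate but not patient-centered. Any disagreement also yields an uncertain result. This stands: the share positive can only be an assumption.

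*Conflict is limited to a band.* The 70% mark passes alone only when agreement lies between 70% and Pe + .41(1 − Pe). Above the band both pass. At 60% positive with an equal split, 70% agreement gives kappa .46 and the marks nearly coincide. With three equal categories, kappa .41 needs only 61% agreement, so the conflict could even run the other way. This also stands: a simple majority of positive items does not produce the problem.

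*Kappa is already planned, and the reliability conclusion is attached to it.* This largely stands, and it limits the severity. But the 70% mark is still given its own conclusion of acceptable reproducibility, and the text does not subordinate it to kappa. That is a rule the article states, not detail it leaves to a fuller document.

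*Kappa alone can mislead under extreme skew.* If each of two panels rates 19 of 20 items positive, with the single exception in the same category but on different items, agreement is 90%, Pe = .9025 + .0025 = .905 and kappa = −.005/.095 = −.05. This stands, and the remedy has to provide for it.

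The choice of kappa weights can fairly be left to a fuller document. Calling the kappa mark conservative is justified in the article by earlier results that are not available here, so that wording is not pressed.

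**Conclusion.** The concern holds in a limited form. The article fixes two stand-alone marks for one question without precedence, and they can conflict when determinations are concentrated in one category. The gap is negligible to small near 60% positive, moderate at 70% and large from about 80%: with 20 items, unrelated panels reach the 70% mark with probability 45-53% at 80% positive and 73-77% at 85%. All of these figures rest on assumed category shares, equal margins in the two panels and an assumed item count. The algebraic limit, chance agreement of at most 49% for 70% agreement to give kappa .41, needs none of these.

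It would go too far to conclude that the criteria will conflict, or that the plan lacks a chance-corrected measure. The defect is that the 70% rule, followed as written, can label unrelated panels acceptably reproducible. This should be fixed; it is not a fatal flaw.

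**What to change.** 1. State that 70% agreement alone does not establish reproducibility, and that the conclusion rests on the already planned kappa, or on both marks being met.
2. Report percent agreement beside its chance-expected value and each panel's category shares.
3. Give kappa with a confidence interval.
4. If nearly all items fall in one category, so that kappa is uninformative, also report between-panel differences in item medians.

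Linear weighting of kappa and removal of the word conservative are optional.

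The cost is a few sentences and a few lines of analysis; no further data are needed. The downside is that the reproducibility result may look less favourable than under the 70% mark alone.

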Second, we will test the new approach using one of the DMD care guideline domains that was developed using RAM but without patient or caregiver input, such as cardiac or endocrine care management guidelines. To do so, we will conduct two 3-round EL panels using a modified version of the EL system to determine the level of patient-centeredness of selected DMD care recommendations already deemed clinically appropriate. Our operational definition of patient-centeredness will be informed by the existing literature and consistent with the operationalization of appropriateness used in RAM. Our 3-round design is consistent with a recommendation for conducting Delphi studies with 2 or 3 rating rounds [42]. In testing the new approach, we will compare participants’ ratings of patient-centeredness, satisfaction levels, and participation rates after rounds 1 and 3 in both panels. Because round 1 of the EL process is essentially a survey, we will treat round 1 ratings as data from a patient engagement survey—a more common mode of patient engagement than the modified Delphi approach [43]. Such a strategy is particularly relevant for comparing the two approaches in a rare disease community where the pool of potential participants is limited. Finally, as in previous studies validating the EL approach [31,39], we will determine the replicability of final panel ratings of patient-centeredness by comparing results of two EL panels conducted using the same protocol.

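### The kappa rule for declaring the online approach reliable is a bare point-estimate cut-off at .41, and the reason given does not support calling it conservative

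*Protocol article*

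**What the plan says.** The Data Analysis section of the protocol article fixes the replicability verdict in advance. Each panel's round 3 ratings of a care strategy are reduced to one determination. Unless the panel disagrees, "the value of the median will determine if the group decision is positive, negative, or uncertain". The plan will then "calculate kappa coefficients comparing the determinations made by the two panels across items", and the rule is: "If the kappa statistic is at least moderate (.41-.60), we will consider the online approach to be a reliable mode of collecting patient-centeredness ratings". The cut-off is defended in one sentence: "This threshold is conservative; previous research shows that the reproducibility of both in-person [51] and online [31] panel findings is rarely better than moderate".

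The items are limited in scope. According to the Abstract, the panels will "rate patient-centeredness of a subset of DMD care management recommendations already deemed clinically appropriate and necessary", and Data Collection says the team will "test the new approach using one of the DMD care guideline domains that was developed using RAM". The article does not say how many strategies will be rated. It does say that patients and caregivers will be asked how many scenarios are acceptable.

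The same Data Analysis paragraph treats 70% agreement between panels as acceptable reproducibility and adds *t* tests with a Wilcoxon sensitivity analysis. The text does not make any of these a joint condition with the kappa rule.

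**The concern.** Two things do not fit together: the label and the rule.

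The label rests on the statement that earlier panels seldom exceed moderate agreement. That is a ceiling on past results. It explains why a higher bar might be unrealistic, but it does not show that reaching the bottom of the moderate band is hard.

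The rule acts on the observed kappa alone. Kappa is computed over care strategies with the two panels as the two raters, so its sample size is the number of strategies. Recruiting 80 to 95 people (20 + 60 to 25 + 70) may raise the true agreement between panels, but it does not remove the item-sampling error. With few items, panels whose true agreement is below moderate can pass by chance, and truly moderate panels can fail.

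At stake is the statement that the method is a reliable mode of collecting ratings. The project hopes to carry its lessons to other clinical areas, so a marginal pass should not be reported as having cleared a strict test.

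**Working it through.** **Inputs from the article.** Cut-off .41 on the observed kappa; three determinations; two panels; kappa taken across items; items are a subset of one guideline domain. The article states no error rate or precision for kappa, so there is no figure of its own to reproduce.

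**Assumptions.** Number of items *n* = 10, 20, 40 or 100. Shares of the three determinations: equal thirds, 60/30/10 or 70/25/5, the same in both panels.

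**Model.** With shares m_i and true kappa k, the chance that the panels give determinations i and j is p_ij = (1 − k)·m_i·m_j, plus k·m_i when i = j. Observed kappa = (po − pe)/(1 − pe), where po is observed and pe chance agreement. For the three share patterns, pe is:
- 3 × (1/3)² = .333
- .36 + .09 + .01 = .460
- .49 + .0625 + .0025 = .555

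**Pass rates.** Share of simulated studies with observed kappa ≥ .41 (200,000 replicates per cell; an undefined kappa counts as a fail), in the order equal thirds / 60/30/10 / 70/25/5:

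| True kappa | 10 items | 20 items | 40 items | 100 items |
|---|---|---|---|---|
| .30 | 28 / 32 / 34% | 22 / 27 / 28% | 16 / 20 / 22% | 7 / 9 / 12% |
| .40 | 43 / 46 / 47% | 43 / 46 / 46% | 44 / 46 / 46% | 44 / 44 / 45% |
| .50 | 60 / 61 / 60% | 67 / 67 / 65% | 77 / 74 / 72% | 90 / 86 / 83% |

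At true kappa .20 the rates are 16–23% at 10 items, 8–15% at 20, 3–7% at 40 and at most about 1% at 100.

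**Precision of a just-passing result.** The large-sample standard error is √[(A + B − C)/n]/(1 − pe), where
- A = Σ p_ii[1 − 2m_i(1 − k)]²
- B = (1 − k)² Σ_{i≠j} p_ij(m_i + m_j)²
- C = [k − pe(1 − k)]²

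For equal thirds, k = .41 and n = 20: A = .223, B = .061, C = .046, so SE = √(.2386/20)/.667 = .164 and the 95% half-width is 1.96 × .164 = .32. The three share patterns give:
- equal thirds: .41 ± .32, about .09 to .73
- 60/30/10: SE .187, .41 ± .37, about .04 to .78
- 70/25/5: SE .209, .41 ± .41, about .00 to .82

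**Adding the 70% criterion.** If both kappa ≥ .41 and agreement ≥ 70% were required, the pass rate at true kappa .30 and 20 items would go from 22% to 10% (equal thirds), from 27% to 24% (60/30/10), and stay at 28% (70/25/5). The reason is that kappa = .41 already implies agreement of pe + .41(1 − pe) = .607, .681 and .737 respectively. With the most skewed pattern, 70% is the weaker condition.

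**The case against.** The other side has several fair points.

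- *Conservative* is used relative to earlier panels. A reader might infer that the protocol claims a low false-positive rate; it makes no such claim. A reader might also infer that the stated reason argues the opposite, with .41 sitting where typical panels already are. The article does not support that either: seldom better than moderate is an upper bound, and it also fits panels that were often only fair. The cited studies are not at hand. What stands is narrower: the reason does not establish strictness.
- Kappa is not the only criterion. The 70% agreement mark helps substantially when the determinations are evenly spread. It is not joined to the kappa rule, though, and hardly helps when the shares are skewed. Skew is plausible because the items are already judged clinically appropriate and necessary.
- The pass rates rest on assumed item counts and shares, and nothing shows that a true kappa of .30 is likely. Determinations are group medians from randomly split panels of more than 40 recruits each, which may push true agreement up. At 100 items the problem at true .30 is much smaller.
- A confidence interval may well appear in a fuller plan. Its absence from the article is therefore not the finding; the stated verdict rule and its label are.
- A tempting remedy is to require a lower confidence limit above .20. Tested at 20 items, that cuts the pass rate at true kappa .50 from about 65% to about 26–41%. It would reject most truly moderate panels, so it is not recommended.

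**Conclusion.** The concern holds in limited form. The article commits to calling the approach reliable on an observed kappa of .41 or more, and its justification does not show that this bar is strict. Over 10 to 40 items and the three share patterns, panels with true kappa .30 pass in about 16–34% of studies. Panels with true kappa .40, just under the cut-off, pass in about 43–47%, and more items do not change that. At 20 items a just-passing kappa cannot exclude agreement well below moderate.

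How often weak panels would pass depends on inputs that the article does not give. It falls to 7–12% at 100 items for true kappa .30, and is small for true kappa .20 once there are 40 items or more. The weakness of the label does not depend on the item count. This affects how firmly the study may word its reliability conclusion, not its design. Severity: minor to moderate.

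**What to change.** 1. Delete the clause that calls the threshold conservative, or replace it with a statement that .41 is the lower edge of the moderate band and is applied to a point estimate.
2. Report kappa with the number of care strategies rated and a 95% bootstrap interval, resampling strategies.
3. Let the interval govern the wording. When it extends below .41, report a moderate point estimate that is compatible with lower agreement, rather than established reliability. Read it alongside the 70% agreement result.
4. Do not add a hard lower-limit cut-off of .20, for the reason given above. The interval should grade the statement, not replace one pass/fail line with another.

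The cost is some wording and a few lines of code, with no extra participants or data. The downside is a less favourable statement when few strategies are rated. At 20 items even an observed kappa of .70 has a lower limit of only about .44 (equal thirds), .40 (60/30/10) or .37 (70/25/5), from half-widths of .26, .30 and .33. The stronger wording would then be reserved for observed values of roughly .7 and above.
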